## Abstract

**Background:**

Lumbar spinal stenosis is the most frequent reason for spinal surgery in elderly people. For patients with moderate or severe symptoms different conservative and surgical treatment modalities are recommended, but knowledge about the effectiveness, in particular of the conservative treatments, is scarce. There is some evidence that surgery improves outcome in about two thirds of the patients. The aims of this study are to derive and validate a prognostic prediction aid to estimate the probability of clinically relevant improvement after surgery and to gain more knowledge about the future course of patients treated by conservative treatment modalities.

**Methods/Design:**

This is a prospective, multi-centre cohort study within four hospitals of Zurich, Switzerland. We will enroll patients with neurogenic claudication and lumbar spinal stenosis verified by Computer Tomography or Magnetic Resonance Imaging. Participating in the study will have no influence on treatment modality. Clinical data, including relevant prognostic data, will be collected at baseline and the Swiss Spinal Stenosis Questionnaire will be used to quantify severity of symptoms, physical function characteristics, and patient's satisfaction after treatment (primary outcome). Data on outcome will be collected 6 weeks, and 6, 12, 24 and 36 months after inclusion in the study. Applying multivariable statistical methods, a prediction rule to estimate the course after surgery will be derived.

**Discussion:**

The ultimate goal of the study is to facilitate optimal, knowledge based and individualized treatment recommendations for patients with symptomatic lumbar spinal stenosis.

## Background

Pain radiating to lower extremities is a frequent complaint, especially in elderly people, and lumbar spinal stenosis is one of the underlying conditions. Lumbar spinal stenosis is defined as "buttock or lower extremity pain, which may occur with or without low back pain, associated with diminished space available for the neural and vascular elements in the lumbar spine"[1]. Narrowing can be localized at three different anatomic structures, the central canal, the lateral recess, or the neural foramina.

Patients complain of neurogenic claudication (pain in the buttocks and lower extremities with or without low back pain provoked by walking or extended standing and relieved by rest and bending forward) that is compatible with a narrowing of the lumbar spinal canal. In some patients Computer Tomography (CT) or Magnetic Resonance Imaging (MRI) can verify a stenosis in the lumbar spinal region, in others not. Vice versa a remarkable proportion of asymptomatic persons older 60 years show substantial narrowing of the spinal canal [2].

The incidence and prevalence of symptomatic lumbar stenosis are unknown. It is estimated from data in the USA that every year 90 out of 100.000 persons older than 60 years undergo lumbar surgery and lumbar spinal stenosis is the most frequent indication for this procedure [3,4]. In the Canton of Zurich with 1.3 Mio (2008) inhabitants we estimate that more than 300 operations on patients with lumbar spinal stenosis are performed every year.

### Treatment modalities

The natural course of spinal stenosis can vary, but is in most patients a relatively stable disorder, with severe disability and neurological deficits developing over time and not rapidly. In the SPORT trial it was reported that in most patients treated conservatively, symptoms did not worsen over four years [5]. A further trial focusing on development of pain over a five year period showed that in 70% of patients pain reached a plateau, in 15% pain increased over time and in 15% pain disappeared spontaneously [6,7].

For patients with moderate or severe symptoms different conservative and surgical treatment modalities are recommended, but knowledge about the effectiveness of these measures is scarce. Most of the studies evaluating non-operative treatments are of low quality and there is a lack of knowledge about the appropriate treatment of these patients [1,8]. There is little evidence that pharmacological treatment, including non-steroidal analgesics, calcitonin, methylcobalamin or intravenous lipoprostaglandin E, provides long-term benefit in patients with lumbar spinal stenosis [1]. A systematic review of the literature yielded insufficient evidence to draw conclusions regarding the effectiveness of physical therapy for lumbar spinal stenosis. In certain subgroups of patients physical therapy and exercise may be beneficial in controlling symptoms of neurogenic claudication in lumbar spinal stenosis, but the evidence that spinal manipulation offers benefit in the treatment is insufficient [1,8].

Epidural injections may have potential benefit and may be tried before surgery, but results about efficiency are mixed [9-13]. Some data suggest that epidural injection of corticosteroids relieves leg pain for a limited time but has no effect on the functional status or the need for surgery after one year [14]. The authors of a systematic review came to the conclusion that evidence is insufficient to recommend epidural injections in patients with spinal stenosis [15].

There is some evidence from randomized trials [5,16,17] and observational studies [18-22] that surgery improves symptoms in patients with spinal stenosis. The therapeutic effectiveness of conservative measures or surgery, as mentioned in the guidelines of the North American Spine Society, should be evaluated by further randomised controlled trials [1]. Such trials, however, as demonstrated in the study by Weinstein [16], are difficult to execute in patients with spinal stenosis. In the aforementioned study, patients with spinal stenosis were randomly allocated to either surgery or conservative treatment. Two years after randomization, only 67% of patients in the surgical group actually received surgery and 43% of those who were assigned to conservative treatment had also undergone surgery. Physicians and/or patients seem to have strong preferences for surgery or conservative therapy impeding the accomplishment of randomised trials [23].

The long term success rates of surgery vary between 45% and 72%, depending on the measured clinical outcome assessed (pain, walking capacity, neurologic symptoms, working ability) [24]. The outcome of surgery depends on a number of different factors. Indicators of postoperative outcome have been evaluated in different populations and the results have been summarized in a systematic review [25,26]. A lower self rated preoperative health-status, comorbidity, depression and limited, preoperative walking ability are strong predictors of an unfavorable clinical outcome.

## Methods/Design

### Study design

This multi-centre prospective cohort study includes patients with neurogenic claudication and radiological findings of lumbar spinal stenosis.

### Objectives

1. To develop a prognostic probability function (prediction rule) in order to predict the further course (one, two and three years after diagnosis) *in patients with lumbar spinal stenosis undergoing surgery.*

2. To develop (a) prognostic probability function(s) (prediction rules) in order to predict the further course (one, two and three years after diagnosis) in *patients with lumbar spinal stenosis treated, at least initially, by conservative measures.*

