### Study sample size

Sample size is calculated for objective one, the development of a prognostic function for patients undergoing spine surgery, one year after surgery. Outcome after surgery will be quantified by the Swiss Spinal Stenosis Questionnaire (SSM)[28] and results will be dichotomized. An improvement of more than 0.5 points on the symptom severity scale and physical function scale in the SSM will be categorized as improved. According to the original publication [28] 0.5 points represents a clinically relevant improvement for the patients (Minimal Clinical Important Difference). We estimate that 60% of all patients with verified diagnosis will undergo surgery and two thirds of these (between 60% and 70%) of patients will show an improvement of more than 0.5 points in both scales (symptom severity and physical function) one year after surgery. To estimate the effect of ten prognostic variables we need roughly 100 patients without improvement, as defined above, after surgery. This leads us to include 350 patients in the study who undergo surgery.

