### Outcome measures (baseline and follow up)

Primary and secondary outcome data will be collected at baseline and at six weeks and six months after the time of treatment onset (surgery for the surgery group and time of enrolment for the nonsurgical group). Long-term outcome data will be gathered after one year and then annually up to three years.

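### Patients who start conservatively and are operated on later have no assigned follow-up clock, so the one-, two- and three-year outcomes Objective 2 needs may not be scheduled for them

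*Protocol article*

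**What the plan says.** **Populations.** In the protocol article, section Objectives, Objective 1 seeks a prediction rule "in patients with lumbar spinal stenosis undergoing surgery", with no limit on when the operation takes place. Objective 2 seeks one for patients "treated, at least initially, by conservative measures". A patient who begins with conservative care and is operated on some months later satisfies both descriptions.

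**Clocks.** Four time origins appear:
- Objectives: "one, two and three years after diagnosis".
- Abstract, Methods/Design: "Data on outcome will be collected 6 weeks, and 6, 12, 24 and 36 months after inclusion in the study".
- Outcome measures (baseline and follow up): treatment onset, explained as "surgery for the surgery group and time of enrolment for the nonsurgical group".
- Study sample size: "the development of a prognostic function for patients undergoing spine surgery, one year after surgery".

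**Expected switching.** The Background, under Treatment modalities, reports from a cited randomised trial that after two years "43% of those who were assigned to conservative treatment had also undergone surgery". For this cohort the sample size section says "We estimate that 60% of all patients with verified diagnosis will undergo surgery", without a time window and without separating initial from delayed operations.

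**The concern.** The population of Objective 2 is fixed by how treatment starts. The outcome section sorts patients by whether they are surgical or nonsurgical and gives each group its own time zero. The two classifications agree for patients operated on straight away and for those never operated on. They disagree for patients who switch.

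Two things are at stake. The first is data collection: if a switcher's visits are re-dated from surgery, questionnaires at one, two and three years from enrolment are no longer scheduled, and no later analysis can recover them. The second is selection: if Objective 2 is then analysed in the nonsurgical group, membership is known only in retrospect. At the consultation where the rule is meant to help, nobody knows who will remain unoperated. Patients leave that group largely because conservative care has not been enough, so the remainder probably gives too favourable a picture of how conservative starters fare.

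**Working it through.** **1. One switching patient on each clock.** Suppose a patient is enrolled at month 0, treated conservatively and operated on at month 8 (an illustrative date).
- Enrolment clock: 6 weeks, then months 6, 12, 24 and 36.
- Surgery clock, in months since enrolment: 8 + 1.4 = 9.4, 8 + 6 = 14, 8 + 12 = 20, 8 + 24 = 32 and 8 + 36 = 44.

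Under the surgery clock alone, nothing falls at months 12, 24 or 36. The nearest visits are at months 14, 20 and 32, which are 2, 4 and 4 months away. Under the enrolment clock alone (the abstract), one year after surgery is month 20, which lies between visits at 12 and 24, so the outcome used to size Objective 1 is not scheduled. Neither clock alone serves both objectives.

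**2. The plan's sample size.** It asks for roughly 100 non-improved patients and 60% to 70% improvement. The surgical number is 100 / 0.30 = 334, 100 / (1/3) = 300 or 100 / 0.40 = 250. The stated 350 is not reproduced exactly, but it gives 350 × 0.30 = 105 to 350 × 0.40 = 140 non-improved. It is a sufficient, rounded-up figure, and the point here does not depend on it.

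**3. How many patients could switch.** Total enrolment implied: 350 / 0.60 = 583. The remaining 40% is 583.3 × 0.40 = 233. Let c be the share of conservative starters later operated on. The documents give no value for this cohort, so 10% to 43% is an assumed range, its top taken from the cited trial.
- If the 60% means surgery at any time, the 233 are never operated on; starters = 233.3 / (1 − c) and switchers = c × starters.
- If the 60% means initial surgery, the 233 are the starters; switchers = 233.3 × c.

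| c | Eventual: starters | Eventual: switchers | Switchers / 350 | Initial: starters | Initial: switchers |
|---|---|---|---|---|---|
| 10% | 259 | 26 | 7% | 233 | 23 |
| 20% | 292 | 58 | 17% | 233 | 47 |
| 30% | 333 | 100 | 29% | 233 | 70 |
| 43% | 409 | 176 | 50% | 233 | 100 |

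**4. Illustration of what the choice does to the answer.** Assume 30% improve without surgery (not in the documents) and use the plan's two thirds after surgery. The formulas are: never-operated only, 0.30; later surgery counted as not improved, (1 − c) × 0.30; course regardless of later surgery, (1 − c) × 0.30 + c × 2/3.
- c = 43%: 30%, 0.57 × 0.30 = 17%, and 0.171 + 0.287 = 46%.
- c = 20%: 30%, 0.80 × 0.30 = 24%, and 0.240 + 0.133 = 37%.
- c = 10%: 30%, 0.90 × 0.30 = 27%, and 0.270 + 0.067 = 34%.

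These figures show only that the handling matters. The never-operated figure looks too good beside the one that counts conversion as failure, yet lies below the course that includes results after surgery. So too favourable refers to the course under conservative care itself. Against the all-inclusive course, the direction depends on the assumed rates.

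**The case against.** The best defence is that Objective 2 is already well worded. It asks for a prognosis, not an effect of treatment, and the course after an initially conservative start may properly include later surgery. A reader might infer that the rule for these patients has no interpretable target, or that surgical improvement is wrongly credited to conservative care. The documents do not support either inference: the wording of Objective 2 names a legitimate target, and no comparative effect of conservative care is planned under it.

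It can also be said that the loss of enrolment-timed visits is inferred. No sentence says that a switcher's clock restarts or that earlier visits stop; the abstract would keep everyone on one schedule from inclusion. The nonsurgical group appears only in a parenthesis about timing and is nowhere declared an analysis population. The study-flow figure is not shown, and the handling of later surgery in the models may sit in an analysis plan. Treatment is recorded at every follow-up visit, so conversions will be known.

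All of this limits the point without removing it. The abstract and the outcome section give different time origins, and neither provides both schedules for a switcher. Recording that an operation took place does not supply an outcome at 12, 24 or 36 months from enrolment. An analysis plan can choose a model or a censoring rule, but it cannot restore questionnaires that were not collected.

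**Conclusion.** The point holds as a conflict of population and time zero between the Objectives, the abstract and the outcome section, with no clock named for patients operated on after a conservative start. The missing enrolment-timed outcomes follow if switchers are moved to the surgery clock. The selection problem follows if Objective 2 is then analysed in a never-operated group. Both are conditional on how the texts are applied.

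The number affected is unknown: about 23 to 176 patients under the assumed 10% to 43% crossover and the two readings of the 60%. A reader might take the cited 43%, and hence 176 switchers, as a forecast. It is only a guide, because it comes from a randomised trial at two years, while here physician and patient choose the treatment. Likewise 17%, 30% and 46% are not estimates: they rest on an assumed 30% rate and combine a two-year crossover figure with a success rate at one year after surgery.

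This should be fixed. It concerns one of two stated objectives, it affects which data are collected, and it does not undermine the sample size for Objective 1.

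**What to change.** - Reconcile the Objectives, the abstract and the outcome section on time zero, and state which schedule applies to a patient who switches.
- Define membership of Objective 2 by the treatment decision at enrolment, with time zero at enrolment.
- For patients later operated on, keep the enrolment-timed questionnaires at 12, 24 and 36 months, in addition to the surgery-timed visits that Objective 1 needs.
- Analyse Objective 2 as the course regardless of later surgery, which matches its wording, and report it beside the predicted probability of conversion to surgery. Do not use a never-operated group as its analysis population.
- State whether the 60% refers to initial or eventual surgery.

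The cost is protocol and analysis wording and a few extra questionnaires for patients who switch. Treatment choice is not touched.

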### Eligibility Criteria and identifying patients

Patients will be recruited in four hospitals in Zurich (University Hospital, University Clinic Balgrist, Schulthess Clinic and City Hospital Triemli). To be eligible for the study the participants must: 1) be aged 50 years or more; 2) have uni- or bilateral neurogenic claudication (defined by pain in the buttocks and/or lower extremities provoked by walking or extended standing and relieved by rest and/or bending forward; 3) have a verified diagnosis of spinal stenosis by Computer tomography or Magnetic Resonance Imaging (criteria are shown in table 1)[27]; 4) have an expected life expectancy of more than one year; 5) be able to give informed consent; 6) be available for follow-up and able to complete questionnaires in German language. Exclusion criteria are: 1) cauda equina syndrome requiring urgent surgery; 2) current fracture, infection or significant deformity (> 15° lumbar scoliosis); 3) current enrolment in another spine related treatment study; 4) clinically relevant peripheral arterial disease (confirmed by vascular specialist in patients without palpable pulses in the lower limb).

**Table 1 T1:** Radiological criteria for lumbar spinal stenosis (L1 to L5)^!^

Location of stenosis	Radiological criteria (L1 to L5)
Central canal stenosis	Antero-posterior diameter of spinal canal ≤12 mm[31], or cross sectional area of dural tube ≤100 mm^2 ^[30]

Lateral recess stenosis	Lateral recess height ≤ 3 mm, or lateral recess depth ≤ 5 mm [32,34,35]

Foraminal stenosis	Foraminal diameter ≤ 5 mm [36]

^1^L lumbar vertebra

### Study sample size

Sample size is calculated for objective one, the development of a prognostic function for patients undergoing spine surgery, one year after surgery. Outcome after surgery will be quantified by the Swiss Spinal Stenosis Questionnaire (SSM)[28] and results will be dichotomized. An improvement of more than 0.5 points on the symptom severity scale and physical function scale in the SSM will be categorized as improved. According to the original publication [28] 0.5 points represents a clinically relevant improvement for the patients (Minimal Clinical Important Difference). We estimate that 60% of all patients with verified diagnosis will undergo surgery and two thirds of these (between 60% and 70%) of patients will show an improvement of more than 0.5 points in both scales (symptom severity and physical function) one year after surgery. To estimate the effect of ten prognostic variables we need roughly 100 patients without improvement, as defined above, after surgery. This leads us to include 350 patients in the study who undergo surgery.

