### Statistical analysis

Epidemiologic data and patients' descriptive data available on continuous scales will be presented with medians, interquartile ranges or means and standard deviations as appropriate. Categorical data will be presented as rates and percentages. Associations of the continuous independent variables with the outcome variables will be reported using simple logistic regressions. Results from univariate analysis will guide multivariable modeling.

Assessment of associations will be performed using multi-variable models including potential confounders along with the independent variables of interest. Prognostic scores will be built using either logistic regression analysis or Cox proportional hazard models. Models will be validated in subsamples by cross validation. Calibration and discrimination of the cross-validated prognostic instruments will be assessed using the Brier Score.

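### The surgical cohort is sized on about ten non-improved patients per variable, and the analysis described assesses the score's optimism but does not correct it, so predictions may be too extreme unless signal is strong

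*Protocol article*

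**What the plan says.** All references are to the Protocol article.

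- **Target of the sizing** (Study sample size): "Sample size is calculated for objective one, the development of a prognostic function for patients undergoing spine surgery, one year after surgery".
- **Basis** (same section): "To estimate the effect of ten prognostic variables we need roughly 100 patients without improvement". The assumed improvement rate is "two thirds of these (between 60% and 70%) of patients will show an improvement", and the result is "This leads us to include 350 patients in the study who undergo surgery".
- **Model** (Statistical analysis): "Prognostic scores will be built using either logistic regression analysis or Cox proportional hazard models".
- **Selection** (same section): "Results from univariate analysis will guide multivariable modeling".
- **Validation** (same section): "Models will be validated in subsamples by cross validation". The Brier score is the only performance measure named, for both calibration and discrimination.

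The sample-size section sets no target for calibration or optimism. The analysis section mentions no penalised estimation, shrinkage factor or recalibration of the final score.

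**The concern.** Ten events per variable is a rule for estimating the effects of variables. The first objective is different: a function that gives an individual patient a probability of improvement, which the Discussion expects to inform the choice of treatment. For that use, the calibration of predictions in new patients matters most.

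Maximum-likelihood coefficients from a modest number of events are on average too large for new patients. High predicted risks come out too high and low ones too low. Cross-validation measures this optimism but leaves the coefficients as they are. The Brier score combines calibration and discrimination in one number, so a calibration slope below 1 need not stand out. Univariate screening adds optimism if more than ten candidates are considered. The section on data to be collected lists many measures: socio-demographic, clinical and several radiological ones, comorbidity, and anxiety and depression.

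What is at stake is the extremes of the predicted range, where a prediction aid is most likely to influence counselling before surgery.

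**Working it through.** **1. Reproducing the plan's figures.** Ten variables × 10 = 100 non-improved patients, as stated. Improvement of 60% to 70% means non-improvement of 30% to 40%.

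| Non-improvement | N for 100 non-improved | Non-improved among 350 | Per variable |
|---|---|---|---|
| 30% | 100/0.30 → 334 | 105 | 10.5 |
| one third | 300 | 117 | 11.7 |
| 40% | 250 | 140 | 14 |

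The step to 350 is reproduced only with an unstated allowance for loss: about 5% at 30% (1 − 333.3/350) or about 14% at one third (1 − 300/350). So ten per variable is the floor of the design, and the planned number sits a little above it before loss.

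**2. Expected shrinkage at this size.** Signal strength is not in the documents, so Nagelkerke R² is assumed to lie between 0.10 and 0.40. With non-improvement φ = 1/3, the largest possible Cox–Snell R² is 1 − exp{2[φ ln φ + (1−φ) ln(1−φ)]} = 0.72, and R²cs = 0.72 × Nagelkerke R². For p parameters and expected shrinkage S, the required size is

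N = p / [(S − 1) ln(1 − R²cs/S)].

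Example with Nagelkerke R² 0.20: R²cs = 0.144. For S = 0.90 and p = 10, N = 10 / [−0.1 × ln(1 − 0.144/0.90)] = 10 / [−0.1 × ln 0.84] → 574. Solving the same equation for S at N = 350 gives the last two columns.

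| Nagelkerke R² | N for S = 0.90, p = 10 | S at 350, p = 10 | S at 350, p = 20 |
|---|---|---|---|
| 0.10 | 1200 | 0.73 | 0.57 |
| 0.15 | 783 | 0.80 | 0.67 |
| 0.20 | 574 | 0.85 | 0.74 |
| 0.30 | 365 | 0.90 | 0.82 |
| 0.40 | 260 | 0.92 | 0.86 |

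The 20 parameters stand for a wider candidate list; the article does not state how many will be screened.

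**3. Simulated calibration slope in new patients.** Settings: 350 patients, one third non-improved, ten prespecified predictors, unpenalised logistic fit, no loss. A slope of 1 is ideal; below 1 means predictions are too extreme.

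| Assumed true c | Median slope |
|---|---|
| 0.63 | 0.61 |
| 0.67 | 0.72 |
| 0.72 | 0.79 |
| 0.76 | 0.84 |

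A separate simulation gave 0.71, 0.77, 0.84 and 0.87 at c of 0.66, 0.70, 0.74 and 0.80. With 20 candidates screened univariately at the same size, these fell to 0.56, 0.68, 0.76 and 0.81.

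On the probability scale, at c = 0.68, the tenth of patients with the worst predictions were given an average 65% risk of non-improvement against a true 57%. The tenth with the best predictions were given 10% against a true 14%.

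**4. Effect of correcting at the same size.** Uniform shrinkage or cross-validated ridge brought the median slope to about 0.95 to 1.13. It lowered the error of the predicted probability in about 70% to 80% of datasets. Root-mean-square error fell by about 5% to 13%, and the Brier score by about 0.001.

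**The case against.** **The article is condensed.** The full protocol and any analysis plan are not shown, and shrinkage is a detail often left to them. Naming logistic or Cox regression does not exclude a penalised fit. This stands: a reader might infer that the investigators decided against shrinkage, but the text shows only that none is described. The point does not rest on that silence alone. The ten-per-variable basis, the univariate guidance and the Brier score as sole measure are choices stated in the article.

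**Nothing is miscalculated.** 10 × 10 = 100 is right, and 350 covers it with some room. This stands too. A reader might infer that 350 is too small. The documents do not support that, because they give no signal strength, and the remedy needs no more patients.

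**Cross-validation already deals with overfitting.** It would reveal optimism, but as described it does not change the coefficients, and the Brier score does not isolate the slope. This objection carries only in part.

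**The benefit is small and uncertain.** At true c = 0.74, one rerun found a 5th to 95th percentile range of the slope of 0.74 to 1.40 after uniform shrinkage, against 0.65 to 1.06 without. The median distance from 1 fell only from 0.165 to 0.121, the slope moved further from 1 in 30% of datasets, and the median Brier score went from 0.1927 to 0.1921. This stands, so shrinkage cannot be said to remove the miscalibration in the one dataset this study will have.

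**The simulations are simplified.** Those with documented settings use logistic models, and the equal-effect normal predictors are a convenience. Cox models were not simulated, so the figures apply to the dichotomised one-year outcome on which the study is sized.

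**Conclusion.** The point holds in limited form. Followed as written, the article leads to a score fitted at 10.5 to 14 non-improved patients per variable before loss, selected with univariate guidance, and assessed but not corrected for optimism. If the true c is about 0.63 to 0.76, the median calibration slope in new patients would be about 0.6 to 0.85 with ten prespecified predictors, and lower with wider screening.

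The size rests on an assumed signal strength. At a Nagelkerke R² of about 0.30 or more with ten parameters, expected shrinkage is near 0.90 and the problem is small. It would therefore go too far to say flatly that 350 patients cannot give a well-calibrated rule. What can be said is that the size has no calibration or optimism target behind it, and that a better estimator is available at the same size. The change is worth making because it is cheap and acts on the individual probabilities the study is meant to deliver, although the expected gain is modest.

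**What to change.** **Statistical analysis section**

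- Fit the final score by penalised regression (for example ridge), logistic or Cox. Alternatively, multiply the fitted coefficients by the cross-validated calibration slope, then re-estimate the intercept (logistic) or the baseline survival (Cox).
- Repeat any univariate selection inside each cross-validation fold, so that the estimated optimism includes the selection step.
- Report the calibration slope beside the Brier score.

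**Study sample size section**

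- Keep 350 surgical patients.
- Define the ten as candidate parameters, counting every category and non-linear term examined, not only those retained.
- State the expected shrinkage at 350 over a range of assumed signal strength, as in the second table above.

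**Cost.** Wording and standard software; no additional patients or data. Predicted probabilities will be somewhat less spread out, and improvement is likely but not guaranteed in the single dataset obtained. If a fuller analysis plan already specifies shrinkage, a cross-reference is enough for that item.
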